## Abstract

**Background:**

The use of lLaparoscopic liver resection in terms of time to functional recovery, length of hospital stay (LOS), long-term abdominal wall hernias, costs and quality of life (QOL) has never been studied in a randomised controlled trial. Therefore, this is the subject of the international multicentre randomised controlled ORANGE II trial.

**Methods:**

Patients eligible for left lateral sectionectomy (LLS) of the liver will be recruited and randomised at the outpatient clinic. All randomised patients will undergo surgery in the setting of an ERAS programme. The experimental design produces two randomised arms (open and laparoscopic LLS) and a prospective registry. The prospective registry will be based on patients that cannot be randomised because of the explicit treatment preference of the patient or surgeon, or because of ineligibility (not meeting the in- and exclusion criteria) for randomisation in this trial. Therefore, all non-randomised patients undergoing LLS will be approached to participate in the prospective registry, thereby allowing acquisition of an uninterrupted prospective series of patients. The primary endpoint of the ORANGE II trial is time to functional recovery. Secondary endpoints are postoperative LOS, percentage readmission, (liver-specific) morbidity, QOL, body image and cosmetic result, hospital and societal costs over 1 year, and long-term incidence of incisional hernias. It will be assumed that in patients undergoing laparoscopic LLS, length of hospital stay can be reduced by two days. A sample size of 55 patients in each randomisation arm has been calculated to detect a 2-day reduction in LOS (90% power and α = 0.05 (two-tailed)).

The ORANGE II trial is a multicenter randomised controlled trial that will provide evidence on the merits of laparoscopic surgery in patients undergoing LLS within an enhanced recovery ERAS programme.

**Trial registration:**

ClinicalTrials.gov NCT00874224.

## Background

Liver resection for colorectal metastasis is the only potentially curative therapy, and has become the standard of care in appropriately staged patients, offering 5-year survival rates of approximately 35-40% [1]. For symptomatic benign lesions and those of uncertain nature or large size, liver resection is also a widely accepted treatment. Within the framework of optimising postoperative recovery and/or producing a shorter length of stay (LOS) in hospital, laparoscopic surgery and enhanced recovery programmes have recently been introduced for liver surgery.

Laparoscopic liver resection was first described in 1995 [2]. Over the past decade the method has gained wide acceptance for various liver resection procedures [3-9]. Multiple retrospective case series and reviews comparing open with laparoscopic liver resection indicate that laparoscopic liver resection can be used safely for both malignant and benign liver lesions [10-15]. Recent publications from expert centers show that a substantial part of the total volume of major and minor liver resections is performed laparoscopically, and results are good [16,17]. Laparoscopic liver resection is associated with shorter LOS, less postoperative pain, earlier recovery, and better quality of life (QOL) [9,13,18,19]. Comparing patients undergoing an open left lateral sectionectomy (LLS) of the liver with those undergoing laparoscopic LLS, both Vigano *et al*. and Carswell *et al*. [20,21] found no significant difference in operating time between the two groups. In addition, the median length of postoperative LOS was significantly less (6 vs. 9 days, *P* ≪ 0.01) after laparoscopic resection [3]. Furthermore, no evidence of a compromised oncologic clearance in laparoscopic liver resection has been found [3,13]. However, recovery and LOS are not only dependent on the type of surgery or procedure, and other variables should also be taken into account.

The Enhanced Recovery After Surgery (ERAS) programme has been introduced to improve postoperative care. This multimodal programme, derived from Kehlet’s pioneer work in the 1990s for multimodal surgical care, involves optimisation of several aspects of the perioperative management of patients undergoing major abdominal surgery. In patients undergoing segmental colectomy, the ERAS programme enabled earlier recovery and consequently shorter LOS [22-25]. Furthermore, a reduction of post-operative morbidity in patients undergoing intestinal resection was reported [26-29]. These results stimulated liver surgeons of the ERAS® group (Maastricht, Edinburgh and Tromsö) to adapt the ERAS programme to patients undergoing open liver resection. Van Dam *et al*. [30] found a significantly reduced LOS after open liver resection when patients were managed within a multimodal ERAS programme. Besides a reduction in median total LOS from 8 to 6 days (25%), the data also suggested that a further reduction in stay could be possible as there was a delay between the recovery and actual discharge of the patients [30]. Moreover, Stoot *et al*. found retrospectively that there was a further reduction in LOS from 7 days to 5 days when patients were operated laparoscopically and managed within an ERAS programme [31]. In that study there was also a delay between recovery and actual discharge of the patients. Previously, Maessen *et al*. reported a median delay to discharge of 2 days after patients had functionally recovered after colonic surgery managed within an ERAS programme [32]. This delay is often linked to patient age, hospital logistics, and absence of social and/or homecare support.

In most reported trials aiming at earlier recovery or a reduction in LOS, type of surgery and/or perioperative management were not standardised. In addition, the added value of laparoscopic LLS compared with open left lateral sectionectomy within an ERAS programme in terms of time to functional recovery, LOS in hospital, costs, and QOL has never been studied in a randomised controlled trial (RCT). However, randomisation of patients undergoing open or laparoscopic liver resection is hazardous. It is to be expected that experienced centres will be reluctant to randomise patients because of the absence of clinical and patient equipoise for laparoscopic resection. To capitalise on both centers with and without preference for laparoscopic liver surgery, and to thereby acquire an uninterrupted prospective series of patients, an alternative trial design with two randomisation arms (open versus laparoscopic surgery) and a prospective registry has been constructed for the ORANGE II trial. The combination of an RCT and a prospective registry will improve overall power and strengthen the external validity and generalisability of study results [33-35].

## Methods

### Ethics approval

The study has been approved by the Medical Ethical Review Board of the Maastricht University Medical Center, Maastricht, The Netherlands trial number NL 25591.068.08 / MEC 08-2-110. Ethics consent will also be obtained from the national or regional ethics boards in each participating country. Patients willing to participate in this trial will receive both verbal and written information at the time of recruitment in the outpatient clinic. In accordance with the local medical ethics committee all participating sites will provide an independent surgeon or physician if needed. An independent surgeon ([name]) has been appointed for the Maastricht University Medical Center to answer questions. Confidentiality is guaranteed by assigning the participators an encoded trial number. This indicates that only the physician with the decoding ‘key’ will know which code number has been assigned to any patient. All trial data will be saved during the trial and stored on a server, and patients will be asked to consent to future analysis of these data. Withdrawal from the trial at any time or for any reason will not hold any form of consequences for the patient, and data from these patients will be deleted.

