### Statistical analysis

#### Sample size

Because laparoscopic liver surgery focuses on accelerated recovery, time to functional recovery is used as the primary outcome parameter. Owing to the lack of hard evidence about the reduction in time to functional recovery after liver surgery, we have chosen to use the parameter that most accurately approaches our primary endpoint for our power calculation (LOS). Based on a retrospective analysis of 31 patients in both ERAS and non-ERAS settings, who have undergone LLS from 1990 to the present time, the mean ± SD post-operative hospital stay for a LLS in the Maastricht University Medical Center is 6 ± 2.73. It therefore seems that that in patients undergoing laparoscopic LLS, time to functional recovery is reduced in comparison to patients undergoing the open procedure. We are aiming for a reduction in time to functional recovery of 2 days. A sample size of 2 × 40 patients in the randomisation arms will be sufficient to show a 2-day reduction with a power of 90% and a level of significance at α = 0.05 (two-tailed, given a within-arm SD of 2.73 with effect size *d* = 0.73). Assuming an expected withdrawal rate of ≤ 10% during the trial, the participation of at least 10 centres, and the required addition of one randomised patient per arm for every additional participating centre (C) to compensate for the loss of degrees of freedom incurred in the data analysis, which takes centre and treatment × centre effects into account, a total sample size of 110 (n = 2 × 55) will be required.

For all secondary outcome measures, the power will be 75% after correction for multiple testing with two-tailed α = 0.01, assuming the same effect size (*d* = 0.73) as for the primary outcome. An interim analysis of the primary outcome, using Snapinn’s method, will be performed after inclusion of 50% of the sample to avoid unnecessary inclusion of too many patients in this ORANGE II trial [56].

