#### Intention to treat

Analysis of all patients will be performed according to the intention-to-treat principle: patients will be analysed as randomised or as planned in the non-randomised prospective registry, and all patients will be included in the data analysis with proper methods for handling missing data.

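### Deleting the data of every patient who withdraws contradicts the promise to analyse all patients as randomised, and could bias the primary comparison

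*Protocol article*

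**What the plan says.** Three statements in the protocol article bear on this.

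- **Ethics approval.** "Withdrawal from the trial at any time or for any reason will not hold any form of consequences for the patient", and the sentence continues "and data from these patients will be deleted". It sets no condition: deletion is limited neither to data after the withdrawal date nor to patients who ask for it.
- **Intention to treat.** "Analysis of all patients will be performed according to the intention-to-treat principle". The same sentence says that "all patients will be included in the data analysis with proper methods for handling missing data". It covers the randomised arms and also the registry, where patients are analysed by planned treatment.
- **Sample size.** "Assuming an expected withdrawal rate of ≤ 10% during the trial" is one of the assumptions behind the total of 110, so withdrawal is an expected event.

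No other part of the article reconciles the first statement with the second.

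**The concern.** A patient whose record has been deleted cannot be analysed as randomised. Missing-data methods do not rescue this, because they work from baseline values and partial outcomes, which deletion removes.

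The timing makes the loss larger than it need be. Functional recovery is scored in hospital until discharge, but questionnaires and cost data run to 12 months after discharge. A patient who tires of questionnaires at 6 months and withdraws would, as written, lose a primary outcome that had been fully observed months before. Any complication or readmission already recorded would go too.

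At stake is the set of patients behind every endpoint. If those who withdraw differ in recovery from those who stay, and do so unequally between arms, the estimated difference is biased. The sample size allowance for withdrawal protects precision and does nothing against bias. For the registry, deletion also breaks into the consecutive series that the design relies on.

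**Working it through.** **1. The plan's own sample size.** Inputs from the Sample size section: difference 2 days ("We are aiming for a reduction in time to functional recovery of 2 days"), SD 2.73 days ("given a within-arm SD of 2.73 with effect size" 0.73), power 90%, two-sided α 0.05.

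- Per arm: n = 2 × (1.960 + 1.282)² × 2.73² / 2² = 39.2, rounded up to 40. This agrees with the stated 2 × 40.
- Withdrawal and centres: 40 / 0.9 = 44.4, rounded up to 45; plus 10 for centres gives 55 per arm, 110 in total. The alternative order also gives 55: 40 + 9 additional centres = 49, and 49 / 0.9 = 54.4.

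The stated figures reproduce, and keeping withdrawn patients' data would not change them.

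**2. Number of patients affected.** 10% of 110 = 11, an upper limit because the plan states the rate as at most 10%.

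**3. Power after deletion.** In a simple two-group comparison that ignores the centre terms, power for a 2-day difference is 0.97 with 55 per arm and 0.95 with 49.5 per arm (55 × 0.9). Power is therefore not the problem.

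**4. Possible bias.** Let a share d of one arm be deleted, and let the mean outcome of those patients differ by k days from that of the patients who remain. The full-arm mean is (1 − d) × m + d × (m + k) = m + d × k, where m is the mean of those who remain. Analysing only those who remain is therefore off by d × k. The documents give no value for k; 0 to 5 days is an assumption. With d = 0.10 in one arm and no deletion in the other:

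| k (days, assumed) | Shift d × k (days) | Share of the 2-day target |
|---|---|---|
| 0 | 0 | 0% |
| 1 | 0.1 | 5% |
| 2 | 0.2 | 10% |
| 3 | 0.3 | 15% |
| 5 | 0.5 | 25% |

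With deletions in both arms, the bias in the difference between arms is the difference of the two products. It is about zero when withdrawal is unrelated to outcome, or when it is equal in amount and kind in the two arms.

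**The case against.** The deletion sentence stands in an ethics section and may repeat approved consent terms. The full protocol and consent form are not shown, and they may make erasure a matter of request. That may be so, but the article states both rules, and they conflict as they stand.

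Several stronger readings are tempting and not supported.

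- **That the article itself predicts withdrawal related to arm.** The Study design section does warn of resentment once allocation is known after postoperative day 3. It speaks of patients with a strong treatment preference, and the consequence it names is poor compliance, not withdrawal. Patients who express an explicit preference go to the registry. Unequal withdrawal remains possible, but the document does not forecast it.
- **That the analysis becomes one of completers only.** Patients who miss visits or questionnaires, or are lost to follow-up without withdrawing, keep their data and remain under the intention-to-treat wording. Only those who withdraw are lost.
- **That no sensitivity analysis could be done.** The article does not say that allocation records are erased, and randomisation runs in web-based software separate from the case record forms. If the allocation counts survive, withdrawals can be counted by arm and extreme-case analyses remain possible. What would be gone is the clinical data needed for anything better.
- **That the shift could reach half the target.** Putting all 11 withdrawals in one arm (11 / 55 = 20%) with k = 5 gives 1.0 day. If withdrawal were unrelated to arm, the chance of such a split is 2 × 0.5¹¹, about 0.1%. It is an extreme case and not an expectation.

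The point about complications is also limited. The Univariate analysis section says that morbidity will be shown as raw data only because the trial is too small to test it, so the harm there is incomplete counts and not a biased test.

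None of this removes the contradiction or the avoidable loss of outcomes already observed.

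**Conclusion.** The concern holds as a contradiction between two stated rules. Followed literally, the deletion rule defeats the promised analysis for up to about 11 of 110 randomised patients and discards primary outcomes and complications observed before withdrawal. A later analysis plan could not restore data already erased.

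Bias is possible, not demonstrated. Under the assumed 0 to 5 day difference and 10% deletion in one arm, it runs from 0 to 0.5 day, or 0 to 25% of the target. The contradiction itself needs no assumption; this range rests entirely on the assumed k and on unequal withdrawal.

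**What to change.** 1. Reword the Ethics approval section: withdrawal ends further participation, data collected up to that point are kept and analysed, and data are erased only when the patient explicitly asks.
2. Report by arm, with timing, how many patients withdrew and how many asked for erasure.
3. Align the Intention to treat section with this, and add a sensitivity analysis for patients whose data were erased.
4. Where an ethics board requires deletion, and for patients who have already consented under the deletion promise, restate the Intention to treat section to say that erased patients are excluded.

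The sample size does not change. The cost is a consent-form amendment through the ethics boards of the participating countries, since approval is sought in each. The new rule can apply only to patients who consent under it, and some of them may still ask for erasure. The change should be made before data are erased, because deletion cannot be undone.

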### Study design

The ORANGE II trial is a prospective superiority study with an experimental design, using two double-blinded randomised controlled arms and a prospective registry to determine whether laparoscopic surgery is to be preferred over open surgery in patients undergoing a LLS and participating in an enhanced recovery programme. In the participating randomising centers, patients, nurses and the ward physician (but not the operating surgeon) will be blinded for the type of intervention up to and including postoperative day (POD) 3. They will record the functional recovery criteria twice daily. Only the investigator and operating surgeons will know the actual procedure. The blinded ward physician(s) will decide on whether a patient will be discharged or not.

However, randomisation of patients undergoing open or laparoscopic liver resection is hazardous as previously explained. Moreover, another potential source of bias exists when randomising patients with a strong treatment preference. When patients cannot be blinded to their treatment allocation (POD 3) they may be resentful and demoralised if they do not receive their preferred treatment, and consequently they may have poor compliance. By contrast, patients receiving their preferred treatment may have above-average compliance.

Thus to capitalise on centres both with and without preference for laparoscopic liver surgery, and thereby to acquire an uninterrupted prospective series of patients, all non-randomised patients undergoing a LLS will be approached to participate in the prospective registry. Registration of these patients is imperative to guarantee a consecutive series of patients and also because the absence of such a series may restrict generalisation of the results, as randomised participants may not in fact be representative [36]. The combination of an RCT and a prospective registry will improve overall power and strengthen the external validity and generalisability of study results [33-35]. This non-randomised registry group will be analysed for centre and centre by treatment interaction as an observational study. Medical centres that wish to participate in this trial, but with liver surgeons early in the laparoscopic learning curve, will be accompanied during the procedure by an experienced proctoring laparoscopic HPB-surgeon.

### Primary & secondary endpoints

The primary endpoint of the ORANGE II trial is time to functional recovery. A patient is fully functionally recovered when all of the following five criteria are satisfied: 1) adequate pain control with oral analgesia; 2) restoration of mobility to an independent level; 3) absence of intravenous fluid administration; 4) ability to eat solid foods; and normal or decreasing serum bilirubin level and international normalised ratio.

It is medically justified to discharge patients when the criteria for full functional recovery are met and if the patient is willing to go home. Secondary endpoints include postoperative LOS in hospital, percentage of readmissions, total morbidity (both general and procedure related), composite endpoint of liver-surgery-specific morbidity, QOL, body image and cosmesis, reasons for delay of discharge after functional recovery, hospital and societal costs over 1 year, and long-term incidence of incisional hernias.

#### Morbidity

The preoperative morbidity status of patients will be measured using the American Society of Anesthesiologists (ASA) scale. The Portsmouth modification of the Physiological and Operative Severity Score for the Enumeration of Mortality and Morbidity (P-POSSUM) will be used to evaluate the risk of perioperative morbidity and mortality. Post-operative morbidity is rationally predictable, with hemorrhagic complications occurring predominantly during surgery or in the early postoperative phase, and biliary complications, intra-abdominal abscess, or liver failure in the later postoperative phase. Wound infection and sepsis will be additional complications that require monitoring. Morbidity will be classified and analysed according to the validated classification for postoperative morbidity as described by Dindo *et al*[37].

#### Liver resection-specific composite endpoint

In this trial, we will also use a well-defined liver surgery-specific composite endpoint, as suggested by van den Broek *et al*. [38]. This endpoint is a parameter composed of a combination of procedure-specific complications, which is considered as a single, dichotomous outcome: operative mortality, intra-abdominal haemorrhage, ascites, bile leakage, intra-abdominal abscess, and post-resectional liver failure. These components, which are all specific to liver surgery and have substantial clinical relevance, reflect complications rated as Dindo grade 3–5. A composite score of 1 (failure) will reflect the occurrence of at least one of the above liver-specific complications, and a score of 0 (success) will be assigned if none of these occur.

#### Quality of life

To assess QOL in patients undergoing laparoscopic versus open LLS, the Dutch version of the EuroQol five-dimension (EQ-5D) status test in Dutch centers and the translated EQ-5D for international centers will be used. The EQ-5D is a standardised instrument for use as a measure of health outcome, which consists of the five dimensions of mobility, self-care, usual activities, pain/ discomfort, and anxiety/depression, with three levels each and a rating on the EQ visual analogue scale (VAS; 0–100). [39-41] Furthermore, the European Organisation for Research and Treatment (EORTC) 30-item post-cancer QOL questionnaire (QLQ-C30; with the liver metastases (LM21) module will be used for liver-specific treatment measurements [42]. Assessment of the patients’ QOL will be performed at the time of consent, discharge and 10 days, 3, 6 and 12 months after discharge.

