#### Body image and cosmesis

To evaluate differences in postoperative body image and cosmesis, the Body Image Questionnaire (BIQ) will be used [43,44], which consists of eight questions about body image and cosmesis. The body image assessment will be performed preoperatively at time of consent. Both the body image and cosmesis assessment will take place at discharge, and at 10 days, 3 months, 6 months and 12 months after discharge.

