#### Incidence of incisional hernias

Incisional hernia after open surgery is a well-known complication of surgery, with an incidence of up to 20% after a 10-year period [46]. In patients undergoing a sigmoid resection, Anderson *et al*. found that laparoscopic resection led to a significantly lower incidence of incisional hernia compared with open surgery [47]. Furthermore, in two retrospectively analysed series of patients who received a partial hepatectomy, different types of incisions were compared. D’Angelica *et al*. reported that the common incisions used for partial hepatectomy were the Mercedes incision and extended right subcostal (ERSC) incision, and that the ERSC incision provides adequate, safe access and is associated with fewer long-term wound complications (9.8% vs 4.8%, *P* ≪ 0.001) [48]. More recently, Togo *et al*. reported frequencies of incisional hernia after median, J-shaped, right transverse incision with a vertical extension at the midline from the subumbilical region to the xiphoid process (RTVE), and reversed T incisions to be 6.3%, 4.7%, 5.4%, and 21.7%, respectively. A diagnosis of ‘no hernia’ required a minimum follow-up of 12 months [49].

To assess the incidence of incisional hernias in patients undergoing laparoscopic and open LLS, they will be contacted at a mean time of 1 year after resection to undergo ultrasonography to assess the incidence of incisional hernia.

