### Functional recovery criteria

The evaluation of time to functional recovery will start on POD 0 and will be scored twice daily until discharge from the hospital. The discharge process starts at the pre-admission counseling session, during which any special needs of the patients will be determined (for example, homecare or social support, transport. Before admittance, any problem that could delay discharge will be identified and addressed. Patients will only be discharged when they have met the functional recovery criteria and are willing to go home. Reasons to delay discharge after functional recovery will be monitored and documented. Functional recovery criteria and LOS in hospital will be independently monitored and analysed.

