#### Univariate analysis

The primary outcome measure of time to functional recovery will be measured in days, and will be analysed with fixed-effect regression that will take centre and treatment × centre interaction into account as fixed effects. If the actual number of centers and the sample size per centre allow random effects analysis, this will also be performed and this analysis will have the same power as the planned fixed effects analysis if the design effect does not exceed 1.2. With a sample size of 10 patients per centre, the design effect is 1.2 if the intraclass correlation (ICC) is 0.02, where the ICC is based on treatment × centre interaction [57].

All secondary outcomes as measured at discharge will be analysed by fixed-effect regression using linear regression for quantitative outcomes and logistic regression for binary outcomes, and including the baseline measure as a covariate to improve power and precision. In addition to *P*-values, confidence intervals for all effects will be reported. Morbidity will be classified as described by Dindo *et al*., but will be presented as raw data only because the required sample size for intervention effects on morbidity is much larger than the calculated sample size for this trial [58].

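### Early quality-of-life and body-image readings are timed from discharge, which laparoscopy is expected to bring forward by 2 days, and the only between-arm regression stated for these scores uses the discharge reading

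*Protocol article*

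**What the plan says.** All references are to the protocol article.

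- **Schedule.** In Quality of life, assessment "will be performed at the time of consent, discharge and 10 days, 3, 6 and 12 months after discharge". In Body image and cosmesis, both are assessed "at discharge, and at 10 days, 3 months, 6 months and 12 months after discharge", with body image alone also measured at consent. No post-operative reading of either is timed from surgery.
- **What fixes discharge.** Functional recovery criteria: "Patients will only be discharged when they have met the functional recovery criteria and are willing to go home". Under Primary & secondary endpoints, those criteria include pain controlled on oral analgesia and independent mobility.
- **Expected effect on discharge.** The abstract assumes that "length of hospital stay can be reduced by two days" with laparoscopy. Sample size aims at the same 2 days for time to functional recovery.
- **Test.** Univariate analysis: "All secondary outcomes as measured at discharge will be analysed by fixed-effect regression", linear or logistic, with the baseline value as covariate.
- **Other uses of the later readings.** Descriptive statistics reports these scores as means and SDs by visit and arm. Hospital and societal costs and Economic evaluation use EQ-5D utilities for QALYs over 12 months.
- **Hernia scan.** Patients "they will be contacted at a mean time of 1 year after resection to undergo ultrasonography". Just before this, the section reports a published series in which a diagnosis of no hernia "required a minimum follow-up of 12 months".

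**The concern.** Discharge is a consequence of treatment. A visit schedule that starts from it gives each arm its own clock, and the clocks differ most if the trial's hypothesis is true. Two things follow for the early readings.

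First, laparoscopic patients answer fewer days after the operation than open patients. If scores improve during convalescence, the faster arm loses part of its advantage.

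Second, at discharge every patient has met the same criteria for pain and mobility. Mobility and pain/discomfort are two of the five EQ-5D dimensions. A quicker recovery then shows up as an earlier discharge and not as a better score at discharge.

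At stake is whether the stated test can show an early quality-of-life benefit if there is one. A null result at discharge could be read as no benefit when the two arms were compared at the same milestone, reached on different days.

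**Working it through.** **Inputs.** The planned reduction in stay is 2 days (abstract; Sample size). The only stay figure given is that the mean "post-operative hospital stay for a LLS in the Maastricht University Medical Center is 6 ± 2.73" days. It comes from 31 retrospective patients in ERAS and non-ERAS settings, and is not labelled as an open-arm ERAS value. Taking 6 days for open and 6 − 2 = 4 days for laparoscopic is therefore an illustration.

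**The plan's own figure.** n per arm = 2 × (1.96 + 1.2816)² × 2.73² / 2² = 39.2, rounded up to 40, with d = 2/2.73 = 0.73. With 10% withdrawal, 40/0.9 rounds up to 45; adding 10 per arm for centres gives 55 per arm, 110 in all. The stated sample size reproduces, and nothing in this point changes it.

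**Timing after surgery.** Day of reading = length of stay + scheduled offset. Relative shift = 2 / open-arm day. Months are taken as 91, 183 and 365 days.

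| Reading | Open | Laparoscopic | Relative shift |
|---|---|---|---|
| Discharge | 6 | 4 | 2/6 = 33% |
| 10 days | 16 | 14 | 2/16 = 12.5% |
| 3 months | 97 | 95 | 2/97 = 2.1% |
| 6 months | 189 | 187 | 2/189 = 1.1% |
| 12 months | 371 | 369 | 2/371 = 0.5% |

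The absolute offset is always 2 days. It matters where scores may change from day to day, which is at discharge and, more weakly, at 10 days.

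**Which readings are tested.** There are five post-baseline quality-of-life readings. Univariate analysis names a regression for one, the discharge reading, which has the largest shift and the common threshold. The other four have summaries by arm and, for EQ-5D, a role in the QALYs, but no between-arm test is stated there.

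**Body image and cosmesis.** The recovery criteria do not score these, so the common-threshold argument does not apply. Only the offset in days does.

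**Could the analysis repair it?** Not for the discharge reading. Days since surgery at discharge are themselves an effect of treatment, so adjusting for them does not restore a comparison on a common day. A later analysis plan can add a model, but not a reading that was never taken.

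**Hernia scan.** The document gives no spread for scan dates. With a mean of 12 months, the share scanned earlier is 50% if dates are symmetric, 52% to 55% if lognormal with SD 1 to 3 months, and 63% for a shifted exponential. All these shapes are assumptions.

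**The case against.** **The later readings are not ignored.** A reader might infer that only the discharge reading is analysed. The document does not support that: later scores are summarised by visit and arm, and EQ-5D feeds the 12-month QALYs. The regression sentence can also be read restrictively, as covering outcomes taken at discharge, with other models left to a fuller document. On that reading it does not sweep in readmission, hernia or one-year costs, which are dealt with elsewhere. This objection stands. What remains is that the article itself places its one stated test for these scores at discharge.

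**Discharge is not a fixed state of recovery.** The Background describes delays between recovery and discharge, with a median of 2 days in a colonic-surgery series, and this trial records reasons for delay. So the criteria set a floor, and patients pass it by varying amounts. That blurs the common threshold but does not remove it. If delays shrank the difference in stay, the timing shift would shrink too.

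**The size is unknown.** One could assume a daily gain in EQ VAS and an SD and turn 2 days into a standardised bias. The document gives neither figure, so that result could not be set against the planning effect of 0.73.

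**The direction is conservative.** Any pull is against laparoscopy, on secondary outcomes, in a superiority trial. True, but it can still hide a benefit the trial sets out to measure.

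**The hernia scan breaches no rule.** A reader might see a contradiction with the 12-month minimum. That minimum belongs to a cited series, and the trial does not adopt it. Scans are timed from resection in both arms, so no bias between arms is shown.

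**Conclusion.** The point holds in a limited form. If the trial's hypothesis is right, the discharge and 10-day readings compare the arms about 2 days apart in time since surgery: day 6 against 4 and day 16 against 14, given the illustrative stays. At discharge, a shared pain and mobility threshold also draws the quality-of-life comparison towards no difference, and this is the reading on which the only stated between-arm regression for these scores rests. The direction rests on scores improving over the early days after surgery and on the overlap between the discharge criteria and EQ-5D; the size cannot be derived from the document.

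At 3, 6 and 12 months the shift is about 2% or less of elapsed time and can be disregarded. The primary endpoint and the sample size of 110 are untouched. The hernia scan is a loosely fixed time point and a minor matter. This is a worthwhile, inexpensive improvement to secondary endpoints.

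**What to change.** 1. Replace the discharge and 10-day readings of quality of life, body image and cosmesis with two fixed post-operative days counted from surgery, the same in both arms. The trial team should choose the days. Keep the 3-, 6- and 12-month visits as they are.
2. Analyse all post-baseline readings of each score in one repeated-measures model, with the baseline value as covariate where one is collected (cosmesis has none), keeping the planned centre terms, and report a treatment contrast with confidence interval at each time.
3. Minor: state the hernia ultrasound as no earlier than 12 months after resection, with a window.

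The cost is a change of schedule wording and a standard model, with no extra patients. Some early questionnaires will fall after the patient has gone home and will need post or telephone. The schedule change has to come before data collection, because readings on a common day cannot be recovered afterwards.
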